### Data collection

Study surveys will be administered online through Alchemer, a HIPAA-compliant survey software platform that stores data in a cloud-based repository which can only be accessed by staff using individual logins and passwords. In addition to a baseline survey, all participants will be asked to complete repeated online surveys administered every three months for a total of 12 months of follow-up post-enrollment (at months 3, 6, 9, and 12). A three-month gap in assessments was chosen to give sufficient time for change to occur in exposure variables without compromising participant recall or retention, or overburdening the participants. Participants will have a total of 60 days to complete each survey from the first date of availability. Participants who miss a survey will be allowed to complete future surveys and will remain in the study unless they request to discontinue participation. Non-fraudulent participants will be compensated $20 in the form of an e-gift card for each completed survey.

Given the risk of mental illness in this population, and survey questions focused on mental health and suicide, procedures have been established to promote the safety of study participants. All participants will be provided with a mental health resource list at the completion of the survey. In addition, survey responses to the Columbia Suicide Severity Rating Scale (C-SSRS) [79] that endorse suicidal ideation with suicide intent or a suicide plan in the last three months will prompt an email alert from the survey software to study clinicians, who are trained in crisis management. Initial outreach will occur within one business day of the email alert to ensure that the participant is safe. Outreach will continue until six contact attempts have been made or the participant is reached, whichever occurs first. Study clinicians will also reach out, up to three times, to emergency contacts if other methods are unsuccessful. Once contacted, study clinicians will assess the participant’s level of risk and conduct safety planning, lethal means counseling, and/or connect the participant to a crisis hotline, as deemed appropriate by the clinical staff member.

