***Mental health***		
Depression	Patient Health Questionnaire-9 (PHQ-9) [80]	9 items on frequency of depressive symptoms (past 2 weeks)
Suicidal ideation and attempts	Electronic Columbia Suicide Severity Rating Scale (eC-SSRS) [79]	11 items on suicidal ideation and behaviors (lifetime^c^ and past 3 months)
Anxiety	General Anxiety Disorder-7 (GAD-7) [112]	7 items on frequency of anxiety symptoms (past 2 weeks)
Post-traumatic stress	Post-Traumatic Stress Disorder Checklist for DSM-5 (PCL-5) [113]	20 items on post-traumatic stress symptoms (past month)
Substance use	Alcohol, Smoking and Substance Involvement Screening Test (ASSIST-Lite) [114]	10 items on substance use and associated impairment (past 3 months)
Alcohol use	Alcohol Use Disorder Identification Test – Concise (AUDIT-C) [115]	3 items on hazardous alcohol use (past 3 months)
Cross-cutting symptoms	DSM-5 Level 1 Cross-Cutting Symptom Measure (DSM-XC) [109]	23 items that assess the presence and severity of 13 symptom domains (past 2 weeks)
Functioning	World Health Organization Disability Assessment Schedule (WHODAS 2.0) [116]	12 items on physical, emotional, and psychological functioning (past month)
Access to and use of services	Adapted from National Survey on Drug Use and Health (NSDUH) [117]	5 items on seeking mental health care (past 3 months)

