***Minority stressors***		
Stigma and discrimination	LGBTQ-Related Stigma and Discrimination Scale [59]	15 items on perceived, anticipated, and enacted stigma due to sexual orientation and/or gender identity (lifetime^c^ and past 3 months)
Intersectional discrimination	Intersectional Day-to-Day Discrimination Index [89]	9 items on general experiences of discrimination (lifetime^c^ and past 3 months)
Childhood adversity	Adverse Childhood Experiences Questionnaire^c^ [90]	10 items on adverse experiences in the first 18 years of life
General stressors	Life Events List (LEL) [91]	22 items on stressful experiences in the past year^c^ (or past 3 months)
Internalized stigma	Revised Internalized Homophobia Scale (IHP-R)^a^ [118]	5 items on negative feelings about sexual orientation (past 3 months)
	Transgender Identity Survey^b^ [119]	18 items on negative feelings about gender identity (past 3 months)

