#### Primary outcomes

The primary outcomes for this study are depression, suicidal ideation, and suicide attempts. Depression will be assessed using the Patient Health Questionnaire-9 (PHQ-9) [80] and suicidal ideation and attempts will be assessed using the electronic self-reported version of the C-SSRS [79]. The PHQ-9 and the CSSR-S are validated screening tools with clinical and research applications, and have previously been used with SGM populations [81–86]. Both are part of the Suicide Prevention Resource Center's Suicide Prevention Toolkit for Primary Care Practices [87]. These assessments are relatively brief, which is expected to improve response and completion rates in the study, and they can also be scaled such that they assess experiences since last assessment. Both assessments include scale scoring that is useful for determining potential severity of symptoms as a means of differentiating risks or monitoring changes over time.

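### Fixed three-month look-backs do not match a 60-day completion window with skipping allowed, so some follow-up time is never asked about for ideation, attempts and exposures

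*Protocol article*

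**What the plan says.** All of this is in the protocol article.

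- **Schedule (Data collection):** "repeated online surveys administered every three months for a total of 12 months of follow-up post-enrollment (at months 3, 6, 9, and 12".
- **Completion window (Data collection):** "Participants will have a total of 60 days to complete each survey from the first date of availability".
- **Skipping (Data collection):** "Participants who miss a survey will be allowed to complete future surveys and will remain in the study unless they request to discontinue participation".
- **Suicidal ideation and attempts (Table 2):** "11 items on suicidal ideation and behaviors (lifetime^c^ and past 3 months". The table footnote limits the lifetime version to baseline.
- **Exposures (Table 2):** for the stigma scale, "15 items on perceived, anticipated, and enacted stigma due to sexual orientation and/or gender identity (lifetime^c^ and past 3 months". The day-to-day discrimination index has the same windows, and the life-events list covers three months at follow-up. The Primary exposures section repeats the three-month window for all three.
- **Depression (Table 2):** "9 items on frequency of depressive symptoms (past 2 weeks".
- **Primary outcomes section, on the depression and suicidality scales:** "they can also be scaled such that they assess experiences since last assessment". Table 2 does not take this up.
- **Data analysis:** Aim 2 uses Kaplan–Meier and Cox models for incident outcomes. Recurrent or persistent depression and ideation are secondary.

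**The concern.** The look-back has a fixed length, but the time between two completed surveys does not. A long interval leaves days that no follow-up item asks about. A short one makes the look-back reach behind the previous survey.

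Unasked time is the more serious problem. It affects two of the three primary outcomes and the time-varying exposures. Because lifetime items are asked only at baseline, no follow-up item listed in Table 2 recovers an attempt that falls in a gap. Run in the usual way, Kaplan–Meier and Cox models carry a participant as at risk and event-free until the next report, unasked days included, which pulls incidence down. The largest gaps belong to late and intermittent responders, and the Discussion concedes that engagement may vary with exposure and outcome. The loss therefore need not be neutral between exposure classes.

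Overlap does less harm. It blurs when an event or exposure occurred and which came first.

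**Working it through.** The plan states no figure on this point, so there is none to reproduce. The check is interval arithmetic, with a month taken as 30 days.

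**Inputs from the article.** Survey k (k = 1 to 4) opens 90k days after enrollment. Its completion delay d_k is between 0 and 60 days. The look-back is 90 days. Anchoring to enrollment is how I read the listed months. **Not in the article:** the distribution of delays and the skip rate. Both are assumed below.

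**1. Consecutive surveys, none skipped.**
Spacing = 90 + (d_{k+1} − d_k), so 90 − 60 = 30 to 90 + 60 = 150 days.
Gap = max(0, spacing − 90) = 0 to 60 days.
Overlap = max(0, 90 − spacing) = 0 to 60 days.

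**2. One survey skipped, the next completed.**
Spacing = 180 ± 60 = 120 to 240 days. Gap = 30 to 150 days, so some gap is certain and overlap is impossible. After two skips, spacing is 210 to 330 days and the gap 120 to 240.

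**3. Enrollment to month 3.**
Spacing = 90 + d_1, so only a gap of 0 to 60 days can arise. Enrollment follows validation of the baseline survey, so overlap cannot pull pre-baseline events into month 3. Any validation delay lengthens the gap.

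**4. Share of follow-up uncovered, no skips.** Follow-up runs to the last completed survey.
- Delay uniform on 0 to 60 days: mean gap 30 in the first interval and 60/6 = 10 in each of the other three. Total 30 + 3 × 10 = 60 days of 360 + 30 = 390, or 15%. Overlap 3 × 10 = 30 days, or 8%.
- Short delays (exponential, mean 10 days, capped at 60): about 10 + 3 × 5 = 25 days of 370, or 7%. Overlap about 15 days, or 4%.

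**5. With skips** (simulation of 20,000 participants per scenario, surveys skipped independently):

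| Assumed delay | Uncovered: 0% skipped | 10% skipped | 20% skipped | Covered twice |
|---|---|---|---|---|
| Mean 10 days | 7% | 13% | 20% | 3–4% |
| Uniform 0–60 days | 15% | 21% | 27% | 5–8% |

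**6. Other anchoring.** If each survey opened three months after the previous completion, overlaps would vanish. Gaps of 0 to 60 days would remain.

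**7. Depression, a separate matter.** Two weeks of recall cover 14/90 = 16% of an on-time interval, whatever the completion window. Surveys at least 30 days apart cannot overlap on a 14-day look-back.

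**The case against.** The strongest case against has five parts.

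- **Double counting.** A reader might infer from the overlaps that incident events are counted twice. The Aim 2 models do not allow it, because each person contributes one first event. Repeat reports can matter only in the secondary recurrent or persistent analyses and in the exposure measures. The planned check of lag and temporality also deals with part of the exposure–outcome ordering. This objection stands, but the lag check does not recover time that was never asked about.
- **Event-free gaps.** A reader might infer that the plan commits to treating gaps as event-free. The article does not say how time at risk, event dates or late surveys enter the models, and such rules often sit in an analysis plan. That stands as to intent. What can be said is how the named models normally behave, and that no later model can supply a question that was not asked. The Discussion's commitment to missing-data methods addresses non-response, whereas a late but complete survey shows no missing item.
- **Wording not fixed.** Table 2 is a one-line summary per instrument, the survey itself is not shown, and Primary outcomes mentions recall since the last assessment. This leaves the suicidality wording uncertain, which is itself a reason to reconcile the two. The remark does not extend to the exposures, whose three-month window is stated twice.
- **Size.** The extremes, 60 of 150 days unasked (40%) or 60 of 90 days covered twice (67%), need day-0 and day-60 completions back to back and are not typical. Nor does a skip always lose three months or more; the range is 30 to 150 days.
- **Recall.** The three-month interval was chosen partly to protect recall, so longer look-backs have a price. This also stands.

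**Conclusion.** The point holds for suicidal ideation, suicide attempts and the time-varying exposures. The article's own schedule and look-backs leave up to 60 days unasked between consecutive surveys, and 30 to 150 days when one is skipped and a later one completed. None of the safeguards it describes recovers that time.

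The range of days follows from the article if opening dates are anchored to enrollment. The share of follow-up lost rests on assumed delays and skip rates: about 7% to 15% with no skips and 20% to 27% with 20% skipped. How many events are missed, and whether the loss differs by exposure class, cannot be worked out from the article.

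Depression should be kept apart. A reader might attribute its limited coverage to the 60-day window, but it comes from the two-week recall. The Data analysis section already speaks of self-reported moderate or severe symptoms, so only the reference to assessment points is lacking.

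**What to change.** **Analysis.** For Aim 2 ideation and attempts, use actual completion dates and fit a grouped or interval-censored survival model, for example a complementary log-log model with log interval length. Take that length as the days the look-back covers, so that time outside any look-back is not credited as event-free. Report the share of follow-up uncovered, overall and by subgroup. This needs no new data if completion dates are kept; the Recruitment section already lists a time-stamp review for the baseline survey. The cost is analysis wording and modest programming. Two limits remain: events inside gaps stay unobserved, and the length term adjusts for time at risk, not for poorer recall.

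**Reconciliation.** Settle whether follow-up items use the fixed windows in Table 2 or the since-last-assessment form mentioned under Primary outcomes. The second would close gaps and overlaps by construction, but recall would vary and could reach about 150 days, or 240 after one skip. The safety alert in Data collection is keyed to the last three months, so any change of wording must be reconciled with it. That makes it a trade-off for the investigators.

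**Depression.** Describe the outcome as new moderate or severe symptoms at a quarterly assessment. This costs one sentence.

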### Sample size

We based our sample size calculations on limited previous studies capturing the prevalence of depression, suicidal ideation, and suicide attempts [1, 4, 7, 33, 63–71] – as well as distal minority stressors [34, 72, 73] – among SGM persons. For Aim 1, using conservative estimates, we expect a sample size of *N* = 500 in each SGM subgroup to provide a minimum of 98% power (normal approximation with continuity correction) to detect a 15% absolute difference in depression prevalence (estimated prevalence ratio of 1.6) between exposed and unexposed persons. We also expect this sample size to provide at minimum 98% power for a 15% absolute difference in both suicidal ideation and attempts. For the LCA, estimates of minimum required sample sizes in growth mixture models with 10 exposure measures ranged from 300 to 1,100 (in a six-class model with low class separation and 20% missing data) based on Monte Carlo simulations [74]. With an estimated 13 indicators of distal minority stressors, our total sample of 2,500 should therefore be adequate for estimating growth mixture models.

All participants will be followed for 12 months with a projected overall retention rate of 80% resulting in *N* = 400 participants in each SGM subgroup available for endline analyses. We will use the same retention procedures successfully implemented in a recent online prospective pilot study with gay men and other men who have sex with men that demonstrated retention rates of 98% at four months [75]. Though retention is not expected to vary by SGM subgroup, our Aim 2 power calculations account for expected variations in terms of the prevalence and incidence of depression and suicide attempts. Drawing on one general population study of depression incidence over a 24-month period [76], we have used a conservative estimate of average annual incidence of one-eighth of the estimated prevalence. We have also extrapolated from existing cross-sectional studies [7, 34, 66, 72, 73, 77, 78] to estimate that between 25–30% of participants will have additional exposures to distal minority stressors over the follow-up period.

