There are several potential drivers of this limited focus on mental health among rural SGM adults. Most importantly, these populations may be harder to identify and reach given rural–urban differences related to identity disclosure, socialization and congregation, and the availability of SGM-specific health services and other resources [40, 99–101]. Our study seeks to address this challenge by drawing upon established methods of online recruitment for SGM populations that can be geotargeted, with the potential to combine these efforts with advertising and recruitment in physical spaces guided by input from our CAB. Secondly, collecting information on suicidal ideation and behaviors has ethical implications given the need to ensure participants’ safety, and represents a greater investment from both researchers and participants in the study. For SGM populations, this can be particularly fraught as there are concerns about unintentionally outing someone when talking to an emergency contact, whether services will be safe or affirming, and the potential for structural stigma to be enacted through different institutions that would be called upon to help ensure safety (e.g., police force, healthcare providers). The REALM CAB, representation of lived experience among the research team, interdisciplinary collaboration, and careful and intensive planning were critical to ensuring that rigorous safety procedures, that take these concerns into consideration, could be established. These resources can help guide future studies that face similar challenges.

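### The stated clinician alert covers suicidal ideation with intent or a plan, but not a suicide attempt reported for the same three months

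*Protocol article*

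**What the plan says.** The Data collection section sets out the safety procedure in some detail. The trigger is defined by C-SSRS responses, namely those which "endorse suicidal ideation with suicide intent or a suicide plan in the last three months will prompt an email alert from the survey software". The alert goes to clinicians trained in crisis management. The timing is fixed: "Initial outreach will occur within one business day of the email alert to ensure that the participant is safe". Outreach continues until the participant is reached or six contact attempts have been made, and then "Study clinicians will also reach out, up to three times, to emergency contacts if other methods are unsuccessful". Risk assessment, safety planning, lethal means counseling and connection to a crisis hotline all come after that contact. One provision does not depend on the alert: "All participants will be provided with a mental health resource list at the completion of the survey".

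The Mental health rows of Table 2 describe the eC-SSRS as "11 items on suicidal ideation and behaviors", asked for the past three months at every survey and for lifetime at baseline only. The Primary outcomes section states: "The primary outcomes for this study are depression, suicidal ideation, and suicide attempts". It names the C-SSRS as the measure for the last two.

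**The concern.** The instrument that drives the alert collects two kinds of information for the same three months: ideation (including intent and plan) and behavior (including attempts). The stated rule acts on the first kind only. Whether someone who discloses a recent attempt is contacted within one business day therefore depends on how they answered other items, and not on the attempt they disclosed.

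What is at stake is participant safety. No estimate, test or power figure changes. The study asks about attempts at baseline and at months 3, 6, 9 and 12, so it already holds the information it would need in order to act.

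**Working it through.** No published figure needs reproducing here. The check is a reading of the text, followed by a simple count of how often the rule applies.

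**Text side by side**

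| Element | Where | Content |
|---|---|---|
| Alert condition | Data collection | Ideation with intent or a plan, last three months |
| What the alert starts | Data collection | Clinician outreach within one business day, up to six contact attempts, then emergency contacts |
| Provision without an alert | Data collection | Resource list for all participants |
| What the eC-SSRS records | Table 2, Mental health | Ideation and behaviors, past three months (lifetime at baseline) |
| Status of attempts | Primary outcomes | Primary outcome, measured with the C-SSRS |
| Other text on safety | Discussion | General statement that rigorous procedures were set up; no alert condition given |

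The recall window of the behavior items equals the window of the trigger. A reported attempt therefore falls inside the period the alert is meant to cover, but no section lists it as a trigger. Take a respondent who reports an attempt in the past three months and answers no to intent and to plan. Under the stated rule no email is sent, no clinician makes contact, and only the resource list is provided.

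Two features of the article suggest that the ideation items should not stand in for the attempt item. The Background describes theories in which ideation and attempts arise from separate processes, and the Data analysis section builds on one of them. The Recruitment section also validates a baseline survey when at least 75% of the survey and of the mental health questions are complete, so an ideation item may be blank when an attempt has been reported.

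**How often the rule is applied**

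Inputs: the enrollment cap of 2,500 (Participants); five surveys, at baseline and months 3, 6, 9 and 12 (Data collection); and 80% projected overall retention at 12 months, giving 400 in each of five subgroups (Sample size), so 400 × 5 = 2,000.

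- Full retention: 5 × 2,500 = 12,500 surveys.
- 80% at every follow-up: 2,500 + 4 × 2,000 = 2,500 + 8,000 = 10,500 surveys.

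Applying 80% at each follow-up is an assumption, since the article gives only the overall 12-month figure. The total would be lower if fewer than 2,500 enroll. It could be higher because the Recruitment section places validation after the baseline survey, so some baseline surveys come from people who are never enrolled. These are counts of surveys, not of missed attempters.

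**Number missed**

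This equals completed surveys × proportion reporting a recent attempt × proportion of those who endorse neither intent nor plan. The article states neither proportion for this cohort, so no number is given.

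**The case against.** The strongest reply is that this is a condensed article. Full alert logic normally sits in a protocol or a safety procedure, the study has IRB approval, and the Discussion refers to careful planning of safety. The sentence also says that certain responses prompt an alert; it does not say that only those responses do. It is possible that attempts are already covered, and that reservation stands. But the article does not leave the topic to another document. It states the condition, window, recipients, timing and number of contacts, and no text supports a further trigger. The Discussion also offers the study's safety resources as a guide for future studies, so a reader could copy the rule as printed.

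A second reply is that the affected group may be very small. The windows coincide, and many people who report an attempt will also endorse intent or a plan. The item wording and skip logic of the electronic form are not shown, so the overlap could be nearly complete. This also stands, and it is why no miss rate is claimed. It does not explain why outreach after a disclosed attempt should depend on other answers.

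A third reply is that more alerts mean more escalation. The Discussion says that "there are concerns about unintentionally outing someone when talking to an emergency contact", and the advisory board helped to shape the procedures with this in mind. The cost is real but limited, because emergency contacts are approached only after direct contact has failed.

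**Conclusion.** The concern holds. As stated, the alert rule is too narrow: it omits a suicide attempt reported on the same instrument for the same three months, although attempts are a primary outcome. The number of participants affected is unknown and may be small. The rule would be applied to roughly 10,500 to 12,500 surveys from enrolled participants if the cap of 2,500 is reached.

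The conclusion rests on reading the printed trigger as the whole rule. Confidence is medium, because a safety procedure that is not shown may already include attempts. In that case the defect lies in the article's text and not in the conduct of the study.

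**What to change.** Make any suicide attempt reported for the past three months on the eC-SSRS an alert condition, both in the Data collection section and in the survey software, followed by the outreach steps already described. Let it act independently of the ideation items, so that a negative or blank ideation answer does not suppress it.

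If attempts are not covered now, the cost is an IRB amendment and one added condition in the existing alert logic. No new survey items are needed, and the existing clinicians can respond. The downside is some additional alerts and a small increase in escalations to emergency contacts, with the risk of outing a participant. If the operating procedure already covers attempts, the cost is one corrected sentence in the article.
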